### Interventions {11a}

The intervention group will receive a structured exercise adapted from the BReast cancer and EXercise (BREX) program which has shown significant improvement in Quality of Life and Physical Fitness among breast cancer survivors [15]. The exercise program will continue for 2 months, and a follow-up will be done after 3 months. The exercise program is detailed in Table 1. Exercise would be prescribed and supervised by the physical therapist (FR and WA). The control group will continue with their routine life and will receive standard care given by the hospital.

**Table 1 Tab1:** Description of the proposed physical rehabilitation program among breast cancer survivors

Components of physical rehabilitation program Supervised—2 times a week Individually tailored program—3 times a week	Frequency (5 times a week for 2 months)
Supervised Training: Two types over alternate weeks: 1) 60-min step aerobics class 2) 60-min circuit training class Each class will include warm-up and cool-down periods both lasting 10–15 min. The maximum target rate of perceived exertion (RPE) would be set at 14–16 on a 20-point Borg scale, a level of exercise that feels “somewhat hard” or “hard” and coincides with about 86–92% of maximal heart rate, 76–85% of maximal VO_2_, and 5–7 metabolic equivalents (METs) ideal for improving the related domains of QoL and cardiovascular endurance [16]. During the first 3 weeks, the participants would exercise at a lower level of RPE (approximately 11–13), to adapt to the training	Twice a week
Unsupervised home program: Home training would consist of endurance training such as walking, Nordic walking, or aerobic training, but it would also include jumps and leaps like step aerobics (96 jumps and leaps per home training session) to promote bone health [15]. Warm-up and cool-down exercises, such as marching or climbing upstairs would be recommended before and after the home training session. Home training would be aimed so that the total training would comprise a minimum of five training sessions per week	Three times a week

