### Allocation of participants and intervention: randomization and blinding {16a} {16b} {16c} {17a} {17b}

Participants would be allocated to two groups, randomized into equal allocation ratio (1:1) using a simple randomization method through a sealed envelope, with 36 randomized to intervention and 36 to control. Randomization for subject allocation would be double-blinded (conducted by a third party not involved in research) and facilitated through a person not involved in the study. Allocation of intervention will not be blinded and conducted by two researchers in the study FR and WA (physical therapists).

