### Follow-up {18b}

All participants in the intervention group would be followed up after 3 months of training sessions. The demographics and primary outcome would be reassessed to analyze the effects on the baseline, at the end of intervention after 2 months and follow-up at 5 months. Any adverse effects at the time of follow-up would also be recorded.

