### Adverse event reporting and post-trial care {22} {30}

If any adverse effects would be noted and immediately reported by the supervising investigators with record maintenance. If required, participants would be given appropriate treatment and post-trial against any harms at the Thumbay Hospital, UAE.

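### As written, adverse effects are looked for more closely in the exercise arm, and at 5 months only there, so exercise harms have no unbiased control rate to be judged against.

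*Protocol article*

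**What the plan says.** All references are to the protocol article.

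- **Follow-up {18b}.** The section opens with "All participants in the intervention group would be followed up after 3 months of training sessions". It then gives the reassessment times as baseline, "at the end of intervention after 2 months and follow-up at 5 months", and ends with "Any adverse effects at the time of follow-up would also be recorded". Only the opening sentence names an arm.
- **Data analysis {20a} {20b} {20c} {21b}.** Unpaired t-tests compare the groups on the primary outcomes. The repeated-measures ANOVA over the three time points is for the intervention group only. No comparison of harms is described.
- **Adverse event reporting and post-trial care {22} {30}.** Adverse effects are to be "immediately reported by the supervising investigators with record maintenance". No arm is named.
- **Interventions {11a} and Table 1.** "Exercise would be prescribed and supervised by the physical therapist", with two supervised and three home sessions a week for 2 months. For the comparator, "The control group will continue with their routine life and will receive standard care given by the hospital".
- **Strategy for Treatment modification and adherence {11b}{11c}.** Home sessions are checked by audio or video call and through a daily logbook. A noted adverse effect is a ground for removing a participant; again no arm is named.
- **Abstract (Methods) and Objective {7}.** Both mention a 3-month follow-up for the study as a whole, with no restriction to one arm.

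**The concern.** A harm rate in a randomised trial can be interpreted only if events are sought in the same way in both arms. Women who have had chemotherapy and mastectomy will have some background complaints whether or not they exercise. If one arm is seen several times a week and asked again at 5 months, while the other has no described occasion for being asked, more of those background complaints will be recorded in the first arm. A surplus of events among exercisers could then reflect closer observation rather than harm. A modest number of exercise events would have no fair control figure beside it.

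There is a possible secondary consequence. Because a noted adverse effect is a ground for removal, unequal noticing could turn into unequal removal. The article does not say whether removal is from the programme or from the trial, so this is a possibility only.

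**Working it through.** No figure in the plan bears on this point, so the check sets the described contacts side by side by arm.

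| Occasion on which an event could be noticed | Exercise arm | Control arm | Section |
|---|---|---|---|
| Supervised sessions | Twice a week for 2 months | None described | Interventions {11a}, Table 1 |
| Calls and daily logbook for home sessions | Yes, call frequency not fixed | None described | {11b}{11c} |
| Outcome assessment after baseline | Yes | At least one, implied by the unpaired t-tests | Data analysis |
| 5-month follow-up with adverse-effect recording | Yes, stated | Not stated; the sentence names the intervention group | Follow-up {18b} |

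**Step 1: the 5-month visit.** The opening sentence of Follow-up {18b}, read with the 2-month and 5-month times that follow, places a visit 3 months after training ends and assigns it to the intervention group. The adverse-effect sentence refers to that follow-up. The repeated-measures analysis, also for the intervention group only, matches this, so the restriction appears in two places. The Abstract and Objective {7} carry no such restriction. The sections therefore do not agree on whether controls are followed to 5 months.

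**Step 2: the programme period.** Taking 2 months as 8 to 9 weeks (an assumption), supervised contacts number 2 × 8 = 16 to 2 × 9 = 18 per exerciser, plus calls and logbook entries. For controls, the article supports at least one assessment after baseline and nothing more. This counts opportunities to notice an event; it does not measure bias.

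**Step 3: who reports.** The adverse-event section gives the task to the supervising investigators. The only supervision of participants described is that of the exercise, by the physical therapists. The allocation section adds: "Allocation of intervention will not be blinded and conducted by two researchers in the study". Reading the supervising investigators as these therapists is an inference, though a reasonable one. If it is right, the people who report events have regular contact with one arm only and know the allocation.

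**Step 4: what follows.** Detection is more intensive in the exercise arm during the programme, and at 5 months it is described only there. The direction of any bias is towards more recorded events in exercisers. Its size depends on the true event rate and on the chance that an event is noticed in each arm. The documents give neither.

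**The case against.** The strongest reply has four parts.

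1. **The adverse-effect rules name no arm.** This is true of the reporting section, the removal rule and the last sentence of Follow-up {18b}. A reader might infer that control events are deliberately left out, or that capture would be almost complete in one arm and almost nil in the other. The text does not support that. It never excludes control events, the unpaired t-tests require a control assessment after baseline at which an event could be mentioned, and three of the five weekly exercise sessions are unsupervised. Nor does the article say outright that the therapists are the only reporters. This part of the reply stands and limits the point to unequal detection.
2. **The wording may be loose.** The timeline and schedule figures are not shown here and may give visits for both arms. That is possible. But the Follow-up and Data analysis sections agree with each other and differ from the Abstract and Objective, so the written text needs reconciling in any case.
3. **A condensed article may leave adverse-event forms and tables to a fuller document.** That is correct, and their absence is not the point here. The point rests on what the article does state: a follow-up rule tied to one arm, with adverse-effect recording attached to it.
4. **No safety comparison is planned.** This is also correct, so no planned test is invalid. Even so, events that are collected and reported will be read against the control arm.

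A reader might also be tempted to express the size as an assumed event rate, or as the upper confidence limit when no events are seen. Neither measures the bias. The first rests on rates the documents do not give. The second depends only on the number of participants and would be the same with equal ascertainment.

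**Conclusion.** The point holds in a limited form. As written, harms would be ascertained more intensively in the exercise arm throughout, and at 5 months only in that arm, so the trial would not yield an unbiased control rate. The conclusion assumes that Follow-up {18b} means what it says about the intervention group and that no control contacts exist beyond those described. If the figures or a fuller protocol show the same 5-month visit for controls, the 5-month part becomes a wording error, and the imbalance during the programme remains. No numerical size can be given. This should be corrected, but it does not undermine the comparison of the primary outcomes at the end of the intervention.

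**What to change.** - State in Follow-up {18b} whether controls are followed to 5 months, and bring that section, the Data analysis section, the Abstract and Objective {7} into agreement.
- Ask the same standard adverse-event question, with the same wording and recall period, in both arms at 2 months (at the outcome assessment) and at 5 months (by telephone for controls if they do not attend).
- Tabulate the answers by randomised arm. These scheduled answers are the basis for any between-arm statement.
- Report events that came to light only through supervised sessions, calls or the logbook in a separate table for the exercise arm, labelled as having no control counterpart.

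The cost is one short form and about one additional brief contact per control participant, at most about 36 contacts (36 controls × 1). It falls to none if controls already attend at 5 months. The 2-month question adds a few minutes to an assessment that the between-group tests already require. No change to the exercise programme or to any clinical rule is involved.

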#### Data management: storage and confidentiality {19} {27}

The raw data would be systematically synthesized into an Excel sheet and stored in the institutional data repository system for further analysis for 3 years. The data would be managed both in soft and hard copies. Any personal information of the participants relating to direct identity would not be used for any purpose, and data confidentiality would be ensured by the investigators.

### Plans for collection, laboratory evaluation, and storage of biological specimens for genetic or molecular analysis in this trial/future use {33}

Not applicable. The study does not include the collection, evaluation, and storage of laboratory data through biological specimens for future use.

#### Data analysis {20a} {20b} {20c} {21b}

The data would be analyzed using the SPSS software package version 29. Descriptive and inferential statistics will be done to test the desired hypothesis. Paired and unpaired *t*-tests would be conducted to analyze the changes in the primary outcomes for within and between group analysis. Repeated measures of ANOVA would be done to determine the changes at baseline, end of intervention, and follow-up for the intervention group. If the trial needs to be terminated due to any reasons, interim analysis would be done for the average period of the trial for all participants and the trial would be terminated on a decision from the senior researchers (AH and PK). No adjusted analysis is planned for this research. Missing data would be analyzed through intention-to-treat analysis.

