### Sample size {14}

The sample size was calculated using the formula for comparison of two means. The outcome variable used was VO_2_ max (cardiorespiratory endurance variable) which was taken from a previous study [13]. The details on sample size calculation are as follows for 95% confidence interval and power set at 80%.

$$\begin{array}{c}N=\frac{2(Z{(1-\alpha/2)+\mathrm{Z\beta})}^2\times\mathrm\sigma^2}{\mathrm d^2}\\N=\frac{2{(1.96+0.84)}^2\times5.9^2}{3^2}\\N=\frac{545.82}9\\N=60.6\end{array}$$

Considering the 20% dropout and loss to follow-up, the total sample size was 72 (36 in each group).

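### The plan rules out adjusted analysis although the primary outcomes are measured at baseline; baseline-adjusted ANCOVA would be more precise than either form of the planned unpaired t-test, at no cost in patients

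*Protocol article*

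**What the plan says.** The data analysis section names paired and unpaired t-tests, which "would be conducted to analyze the changes in the primary outcomes for within and between group analysis". Repeated-measures ANOVA is planned for the intervention group only, so the unpaired t-test is the only between-group method named. The section then states "No adjusted analysis is planned for this research".

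The follow-up section provides the baseline data: "The demographics and primary outcome would be reassessed to analyze the effects on the baseline", with further assessments at 2 and 5 months. The outcomes are cardiorespiratory health and quality of life, the latter by the EORTC QLQ-C30.

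On size, "The sample size was calculated using the formula for comparison of two means", applied to VO2 max with SD 5.9 and difference 3. The formula has no term for a baseline correlation. The article does not say whether 5.9 is the SD of a post-treatment value or of a change. The trial is to randomise 36 per group, allowing for 20% loss.

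**The concern.** For a continuous outcome that is also measured before treatment, the baseline value usually predicts the later value. A linear model with group and baseline removes the part of the outcome variance that baseline explains. It also corrects the estimate for chance baseline differences in proportion to that prediction. Such differences are plausible here, with simple randomisation, no stratification mentioned, and about 29 to 36 patients per arm.

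The two possible t-tests handle baseline less well. A t-test on 2-month values ignores it. A t-test on change scores subtracts it in full, which over-corrects whenever the correlation is below 1 and the SDs are equal.

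What is at stake is the width of the confidence interval and the chance of detecting the target difference, in a trial that is already short of power on its own inputs. The plan also leaves open which t-test is meant. Naming one model would close off a choice made after seeing the data.

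**Working it through.** **Inputs from the protocol article.** Difference 3, SD 5.9, two-sided 5% level (1.96), 80% power (0.84), 36 per group, 20% loss (sample size section); 1:1 allocation (allocation section). Expected completers per arm: 36 × 0.80 = 28.8.

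**Assumptions.** The baseline-to-follow-up correlation r is not given; I take 0.5 to 0.7 and show 0.3 and 0.8 as well. The SD is taken as equal at baseline and follow-up, and r as equal in both arms. The meaning of 5.9 is not stated, so both readings are worked.

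**The plan's own figure.** 2 × (1.96 + 0.84)² × 5.9² / 3² = 545.82 / 9 = 60.65, which agrees with the stated 60.6. In this formula that is the number per arm. The plan's 72 follows only if 60 is taken as the total: 60 × 1.2 = 72.

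**Power of the unadjusted test on post-treatment values.** Standard error = 5.9 × √(2/28.8) = 1.555. Noncentrality = 3 / 1.555 = 1.93. With 55.6 degrees of freedom the critical value is 2.00, and noncentral-t power is 0.47. With no loss (36 per arm) it is 0.57.

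**Variance of the treatment difference relative to that test.**

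- Post-value t-test: 1
- Change-score t-test: 2(1 − r)
- ANCOVA: 1 − r²
- ANCOVA relative to change score: (1 − r²) / [2(1 − r)] = (1 + r)/2

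| r | ANCOVA reduction vs post value (r²) | ANCOVA reduction vs change score ((1 − r)/2) |
|---|---|---|
| 0.3 | 9% | 35% |
| 0.5 | 25% | 25% |
| 0.6 | 36% | 20% |
| 0.7 | 49% (51% of the variance remains) | 15% |
| 0.8 | 64% | 10% |

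The 51% quoted as the upper end of the range against the post-value test is the variance that remains at r = 0.7; the reduction there is 1 − 0.51 = 49%.

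**Power at 28.8 per arm, 5.9 read as the post-treatment SD.** Effective SD is 5.9√(2(1 − r)) for change and 5.9√(1 − r²) for ANCOVA.

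| r | Post value | Change score | ANCOVA | ANCOVA n per arm for 80%: 60.65(1 − r²) |
|---|---|---|---|---|
| 0.3 | 47% | 36% | 51% | 55.2 |
| 0.5 | 47% | 47% | 59% | 45.5 |
| 0.6 | 47% | 56% | 66% | 38.8 |
| 0.7 | 47% | 69% | 76% | 30.9 |
| 0.8 | 47% | 85% | 88% | 21.8 |

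**Power at 28.8 per arm, 5.9 read as the SD of change.** The change-score test has 47% power at every r. The ANCOVA SD is 5.9√((1 + r)/2):

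- r = 0.5: SD 5.11, power 59%
- r = 0.6: SD 5.28, power 56%
- r = 0.7: SD 5.44, power 54%

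Under this reading the gain shrinks as r rises.

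**The case against.** An unadjusted t-test is a legitimate prespecified analysis. Under randomisation both forms are unbiased, and chance imbalance is already reflected in the standard error. The sentence on adjusted analysis may have been meant for supplementary covariate models only, and saying that none is planned is weaker than a prohibition. All of this stands, and it limits the point to efficiency. It does not remove the point, because the article names no other between-group method and its statement on adjustment is explicit rather than a detail left out for brevity.

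A reader might infer that the plan gives away most of its precision. The document does not support that. It gives no correlation, and more than half of the variance is lost only if the t-test uses post-treatment values alone and r exceeds about 0.71 (r² > 0.5). The wording speaks of changes, so the more natural reading is a change-score test that already uses baseline. Against that test the loss is (1 − r)/2, never more than half for r of 0 or above.

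A reader might also infer that chance baseline differences are simply left in the result. That describes only the post-value test; the change score subtracts them.

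Finally, a reader might treat ANCOVA as the cure for the power shortfall. It is not: at r = 0.7 it needs 30.9 per arm against 28.8 expected.

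**Conclusion.** The point holds as one of efficiency. The plan declines to adjust for a baseline it collects. Apart from the loss of one degree of freedom, ANCOVA is more precise than either t-test for any correlation strictly between 0 and 1. The direction of the gain is secure, but its size is not, because it rests on an assumed r and on an unstated meaning of 5.9.

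For r of 0.5 to 0.7, ANCOVA gains 12 to 29 percentage points of power over a post-value test (59 − 47; 76 − 47). Over a change-score test it gains 12 to 7 points with 5.9 as the post-treatment SD (59 − 47; 76 − 69), and likewise 12 to 7 points with 5.9 as the SD of change (59 − 47; 54 − 47). Power stays below the stated 80% throughout this range. The power figures concern VO2 max only; the article gives no sizing inputs for quality of life.

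The change is worth making because it costs nothing. It is secondary to the sample-size error, which must be corrected in its own right.

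**What to change.** Replace the sentence that no adjusted analysis is planned with wording such as:

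> The primary between-group comparison is the difference at 2 months from a linear model with group and the baseline value of the same outcome (ANCOVA), reported with 95% CI; the same for each QoL scale.

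Keep the unadjusted t-test as a supportive analysis, and state whether it uses 2-month values or changes from baseline. In the sample size section, say whether 5.9 is the SD of a post-treatment value or of a change.

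The cost is wording only. The model runs in the stated SPSS package and uses data already scheduled for collection, with no added patients or visits. Correct the sample-size section separately, and do not offer ANCOVA as a substitute for that correction.

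### The plan names intention-to-treat as its missing-data method; it is not one, and other sections exclude randomised participants' data

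*Protocol article*

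**What the plan says.** All of this is in the protocol article.

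- **Data analysis {20a} {20b} {20c} {21b}**, on missing data: "Missing data would be analyzed through intention-to-treat analysis".
- The same section, on the tests: "Paired and unpaired *t*-tests would be conducted to analyze the changes in the primary outcomes for within and between group analysis", and "Repeated measures of ANOVA would be done to determine the changes at baseline, end of intervention, and follow-up for the intervention group". It adds: "No adjusted analysis is planned for this research". It names no imputation, likelihood-based model or assumption about the cause of missingness.
- **Sample size {14}** expects loss: "Considering the 20% dropout and loss to follow-up", leading to 72 participants, 36 per group.
- **Follow-up {18b}** sets assessments at baseline, 2 months and 5 months, but describes the later follow-up as being for the intervention group.
- **Strategy for Treatment modification and adherence {11b}{11c}** provides for removing participants after a change in medical condition, an adverse effect or a decision to leave.
- **Concomitant care {11d}** leaves out of the analysis the data of any participant, in either group, whose activity matches the intervention's exercise programme.

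**The concern.** Intention-to-treat and missing-data handling answer different questions. The first fixes the analysis set: everyone randomised, in the group assigned. The second says how an outcome that was never measured enters the estimate, and under what assumption. The protocol puts the first in the place of the second, so an analyst who follows the sentence has nothing to implement and falls back on what the named tests do by default, which is to leave out participants without the required values.

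Two things are at stake. A report could claim an intention-to-treat result when only observed cases were analysed. And in an exercise trial, people may leave for reasons linked to fitness or tolerance, so those observed may differ from those randomised. The removal and exclusion rules add to this, because they act after randomisation on grounds that may themselves be related to the outcome.

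**Working it through.** **Inputs.** From Sample size {14}: SD 5.9, difference 3, multipliers 1.96 and 0.84, 20% loss, 72 in total, 36 per group. From Follow-up {18b}: three visits. From the data analysis section: the tests quoted above.

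**The plan's own figure.** 2 x (1.96 + 0.84)^2 x 5.9^2 / 3^2 = 545.82 / 9 = 60.65, which reproduces the stated 60.6. The total of 72 follows as 60 x 1.2. (The formula gives a number per group, which is a separate matter and is not pursued here.)

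**What each named test requires.**

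- Paired t-test: both values of the pair.
- Unpaired t-test on change: an observed change, so a baseline and a later value.
- Classical repeated-measures ANOVA: all three visits. A participant with baseline and 2-month values but no 5-month value is dropped.

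None of the three gives a participant with a missing value a place in the analysis.

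**How many are affected at 20% loss.**

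- Overall: 0.20 x 72 = 14.4 lost, 57.6 left, or 28.8 per arm.
- ANOVA, intervention group only: 0.20 x 36 = 7.2 lost, 28.8 left.
- Between-group t-test at 2 months: this depends on when people leave. If all loss falls before month 2, about 58 remain. If all of it falls after month 2, all 72 remain. The document does not give the timing.

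**Precision, worst timing.** With difference 3 and SD 5.9, normal-approximation power is 57.8% at 36 per arm and 49.1% at 29 per arm (noncentral t: 56.7% and 47.7%). Loss alone therefore costs at most about 9 points (57.8 - 49.1 = 8.7). The rest of the gap to 80% is the separate sample-size matter.

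**Bias, illustration only.** Suppose a fraction d of the intervention arm is lost, their mean change is g units below that of those who stay, and control loss is unrelated to outcome. If those who stay have mean c, the full-arm mean is (1 - d)c + d(c - g) = c - dg, so the observed-case estimate is too high by d x g. Neither d in one arm nor g is in the document. With assumed d of 0.10 to 0.30 and g of 1.5 to 5.9, the result runs from 0.10 x 1.5 = 0.15 to 0.30 x 5.9 = 1.77 units, against a planned difference of 3. At d = 0.20 and g = 3 it is 0.6. It is zero if loss is unrelated to outcome, and reverses if those who leave do better.

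**Sections side by side.** Intention-to-treat keeps every randomised participant in the assigned group. Concomitant care {11d} excludes data because of what a participant did after randomisation; both cannot hold for the same analysis. The treatment modification section does not say whether a removed participant also stops being measured, or whether data already collected are kept, so it may or may not be compatible.

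**The case against.** The protocol never says that only completers will be analysed. The statistical analysis plan is not shown and may specify imputation, and trialists sometimes use intention-to-treat loosely to mean that missing values will be filled in; t-tests and ANOVA can be run on imputed data. This stands as a limit: the available-case result is an inference from how the named tests work. It does not rescue the sentence, which supplies an answer on missing data, and the wrong kind of answer.

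A reader might infer that about 14 of 72 participants disappear from every test. The documents do not support that. The 20% covers all dropout and loss to follow-up; anyone lost after month 2 still enters the 2-month t-tests, and the ANOVA involves only the 36 intervention participants.

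A reader might also attach a definite bias to the plan, such as a fixed share of the 3-unit difference. Nothing in the document gives the dropout mechanism, the split between arms or the correlation between visits, so no such figure can be drawn from it.

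Two further objections bear on the remedy, and both stand. If loss depends on the unobserved outcome itself, a missing-at-random model does not remove the bias, and a participant lost before month 2 contributes only a baseline value. And a three-visit model in both arms needs control measurements at 5 months, which the follow-up section does not clearly provide. A mixed model is also not the only acceptable choice: multiple imputation before the planned tests could serve.

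**Conclusion.** The point holds in a limited form. The missing-data sentence is wrong as stated, the tests named supply no method in its place, and the exclusion in the concomitant care section contradicts the intention-to-treat label; the removal rule sits badly with it. The firm numerical consequence is the loss of about 7 of 36 from the intervention-group ANOVA, assuming the planned 20% applies equally to that arm. For the 2-month between-group comparison the number lost lies between none and about 14 of 72, depending on timing. The size and direction of any bias are unknown. The protocol should be changed, but the point does not show that the trial's result will be biased.

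**What to change.** Replace the sentence with wording such as:

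> All randomised participants are analysed in their assigned group. The between-group comparison at 2 months uses a linear mixed model for repeated measures (group, visit, group-by-visit) on all available values at visits measured in both arms, under a missing-at-random assumption; the 5-month visit is included only if it is also measured in controls. A sensitivity analysis uses multiple imputation with imputed intervention-arm values shifted downward (delta adjustment).

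The sensitivity analysis matters because the main model cannot correct for loss that depends on the unobserved outcome. The model adds no baseline covariates beyond group and visit, so it need not conflict with the statement that no adjusted analysis is planned.

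Then reconcile the other two sections with this analysis set. For example, move the exclusion for matching exercise to a secondary per-protocol analysis, and state that data already collected from removed participants are kept. When participants should stop the programme is a clinical matter and is not addressed here.

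The cost is protocol wording, a little more programming in the stated software, and reliance on a missing-at-random assumption that is at least stated and tested. Restricting the model to visits measured in both arms requires no new data collection.
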